## Abstract

**Background:**

Advances in the understanding and management of pulmonary arterial hypertension have enabled earlier diagnosis and improved prognosis. However, despite best available therapy, symptoms of exertional dyspnoea and fatigue are commonly reported and result in a reduced capacity to perform daily activities and impaired quality of life. Exercise training has demonstrated efficacy in individuals with other respiratory and cardiovascular diseases. Historically, however, exercise training has not been utilised as a form of therapy in pulmonary arterial hypertension due to the perceived risk of sudden cardiac death and the theoretical possibility that exercise would lead to worsening pulmonary vascular haemodynamics and deterioration in right heart function. Now, with the advances in pharmaceutical management, determining the safety and benefits of exercise training in this population has become more relevant. Only three studies of supervised exercise training in pulmonary arterial hypertension have been published. These studies demonstrated improvements in exercise capacity and quality of life, in the absence of adverse events or clinical deterioration. However, these studies have not utilised an outpatient-based, whole body exercise training program, the most common format for exercise programs within Australia. It is uncertain whether this form of training is beneficial and capable of producing sustained benefits in exercise capacity and quality of life in this population.

**Design/Methods:**

This randomised controlled trial will determine whether a 12 week, outpatient-based, supervised, whole body exercise training program, followed by a home-based exercise program, is safe and improves exercise capacity and quality of life in individuals with pulmonary arterial hypertension. This study aims to recruit 34 subjects who will be randomly allocated to the exercise group (supervised exercise training 3 times a week for 12 weeks, followed by 3 sessions per week of home exercise for 12 weeks) or the control group (usual medical care). Subjects will be assessed at baseline, 12 weeks and 24 weeks.

**Discussion:**

This study will determine whether outpatient-based, whole body exercise training is beneficial and safe in individuals with pulmonary arterial hypertension. Additionally, this study will contribute to clinical practice guidelines for this patient population.

**Trial registration:**

Australia and New Zealand Clinical Trials Register (ANZCTR): ACTRN12609000502235

## Background

Pulmonary arterial hypertension (PAH) is characterised by pathological changes in the pulmonary vasculature that cause an increase in pulmonary vascular resistance (PVR) thereby restricting blood flow through the pulmonary circulation [1,2]. To maintain blood flow, pulmonary artery pressure (PAP) increases [2]. Disease progression leads to right ventricular dysfunction and right heart failure [3,4]. The physiologic response of the pulmonary vasculature to exercise is markedly different from normal in individuals with PAH [1,5]. The pulmonary arteries and arterioles have an impaired capacity to vasodilate and distend, and the increase in cardiac output required to accommodate the metabolic requirements of exercise is limited [1]. As a result, oxygen delivery to the peripheral muscles is impaired [6], contributing to the symptoms of muscle fatigue and dyspnoea [1,5]. Whilst the impairment in cardiac output to meet peripheral oxygen demands during exercise largely contributes to the reduction in exercise capacity [7], skeletal muscle dysfunction may also be implicated in the exercise limitation experienced by individuals with PAH [7-10]. Several studies have demonstrated significant morphological and functional changes in skeletal musculature [8-13], which may be related to the decrease in systemic oxygen transport [7]. Changes such as muscle atrophy, decreased oxidative enzymes and increased proportion of type II muscle fibres lead to the early onset of lactic acidosis and a reduced aerobic capacity [7,9,10]

Despite advances in pharmaceutical therapies, which have resulted in improvements in exercise capacity, haemodynamics and outcome in patients with PAH [14], exertional dyspnoea and fatigue continue to result in difficulty performing activities of daily living, lead to the avoidance of physical activity and adversely impact on health-related quality of life (HRQoL) [15]. This inactivity and the resultant physical deconditioning are likely to further exacerbate the functional limitations associated with PAH [8].

Whilst there is a paucity of studies in the PAH population, the benefits of exercise training in individuals with other cardiopulmonary conditions are well established. Specifically, improvements in symptoms, exercise capacity, peripheral muscle function and HRQoL are well documented following exercise training in chronic left-sided heart failure [16-19] and in chronic obstructive pulmonary disease (COPD) [20-23], populations that both report exertional symptoms similar to PAH. These benefits have been achieved following supervised exercise training, 2 to 3 times per week for a period of 6 to 12 weeks, which comprised endurance exercise at a target intensity of between 40 and 80% of peak exercise capacity (peak oxygen uptake [VO_2_] or maximum heart rate [HR]) [16,17,19-21]. In COPD, programs of 12 weeks duration have been shown to produce greater and more sustained improvements in exercise outcomes when compared to programs of shorter duration [20,21].

Historically, exercise training has been discouraged as a therapy for patients with PAH due to the perceived risk that exercise could lead to sudden cardiac death or worsening pulmonary vascular haemodynamics, acceleration of vascular remodelling and deterioration in right heart function [15]. Some evidence exists to suggest that exercise training can be performed without adverse events or detriment to cardiac function or pulmonary haemodynamics [10,15,24,25], however, the efficacy of exercise training in PAH warrants further investigation [14]. To date, only three prospective studies of exercise training in PAH populations have been published [10,15,25]. These studies recruited subjects with idiopathic PAH or chronic thromboembolic pulmonary hypertension, who were stable on medical therapy and were in WHO functional classes II to IV. The exercise training regimen varied in these studies in terms of the frequency of sessions each week (ranging from 3 to 7), duration (7 to 15 weeks) and the exercise modalities [10,15,25]. The types of exercises performed included cycle ergometry [10,15,25], walking [15,25], peripheral muscle training (i.e. quadriceps) [10], breathing exercises [15,25], upper limb exercises [15,25], yoga [15] and mental conditioning [15]. All three studies demonstrated significant improvements (p < 0.001) in exercise tolerance as measured by an increase in 6-minute walk distance (6MWD) [15,25] or endurance time on a cycle ergometer [10], one study reporting improvements in muscle strength and endurance [10]. Improvements in HRQoL (SF-36 component summary scores) were also reported in one study (p < 0.05) [15]. No adverse events were reported in any of the studies.

The studies to date have demonstrated improvements in exercise capacity in this patient population [10,15,25], however these studies have some limitations in the application of exercise training in Australia. Uchi et al [25] recruited subjects who had recently commenced intravenous PAH therapy and thus it is not possible to differentiate between the benefits of exercise and those attributed to the medication. The training programs have included a variety of modalities such as mental training and yoga [15], interventions that do not form part of most cardiopulmonary rehabilitation programs. Within Australia, most rehabilitation programs designed for cardiac or respiratory populations consist of whole body exercise training and take place in hospital outpatient departments or in community settings [26,27]. This contrasts with the study by Mereles et al [15] in which subjects were admitted for a 3 week inpatient training program prior to performing a 12 week home exercise program. In Australia, the resources for providing inpatient exercise training to individuals who are stable on medical therapy are limited [24]. The study by de Man et al [10] evaluated a 12 week outpatient exercise training program which comprised cycling and quadriceps training. The specificity of lower limb exercise training in this study is likely to account for the large increase in endurance cycle time and may explain the non-significant improvement in 6MWD.

To date, the studies have only reported the immediate effects of exercise training and thus it remains unknown whether the benefits are maintained following cessation of supervised training. It is also unknown whether an outpatient-based, whole body exercise training program is beneficial in patients with PAH and whether this type of program is capable of producing sustained benefits in exercise capacity and HRQoL.

This study aims to investigate the benefits of a 12 week hospital outpatient-based, individualised exercise training program involving supervised exercise sessions, followed by a 12 week home exercise program, for a cohort of subjects with PAH.

We hypothesise that:

(i) A 12 week individualised, whole body exercise training program will improve:

• Exercise capacity (as assessed by peak VO_2_; anaerobic threshold; endurance time measured during the constant-workload cycle ergometry test)

• HRQoL

(ii) Exercise training is safe and improvements in exercise capacity will be achieved without evidence of clinical worsening

(iii) An additional 12 week home exercise program will maintain or further improve the benefits gained during the 12 week, supervised, outpatient program.

## Design/Methods

### Design

This study is a prospective, single blind, randomised controlled trial.

### Participants

Thirty-four subjects will be recruited from the Western Australian State Pulmonary Hypertension Service, at Royal Perth Hospital, Perth, Western Australia.

#### Inclusion/Exclusion Criteria

Subjects will be included in the study if they: have a confirmed diagnosis of idiopathic or familial PAH or PAH associated with connective tissue disorders, based on elevated pulmonary artery pressures measured by right heart catheterisation at rest; are in WHO functional class II or III (receiving PAH-specific pharmaceutical therapy); are medically stable and have been on PAH-specific pharmaceutical therapy for 3 months prior to enrolment into the study, and, are willing to complete the supervised and home exercise training programs. Medical stability will be defined as the absence of recent changes in: specific PAH therapy (no change in sildenafil citrate dose for 6 weeks, no change in endothelial antagonist receptors for 3 months); inotropes (including digoxin) and diuretics; symptoms (including dyspnoea and fatigue); body weight and co-morbid conditions.

Subjects will be excluded if they have: oxygen therapy requirements; significant musculoskeletal disease, claudication pain, neurological or cognitive impairment, psychiatric/psychological or mood disorders that may affect their ability to undertake exercise testing or training; a history of moderate or severe chronic lung disease; cardiac disease associated with cardiac failure, poorly controlled angina, unstable cardiac rhythm; involvement in a supervised exercise training program within the last 12 months.

### Recruitment and Randomisation

The flow of subjects through the study is based on recommendations from the Consolidated Standards of Reporting Trials (CONSORT) statement [28] and outlined in Figure 1. Subjects will receive written and verbal information regarding participation in the study and written consent will be obtained from all subjects. The Human Research Ethics Committees of Royal Perth Hospital and Curtin University have approved this study. The study protocol has been registered with the Australian New Zealand Clinical Trials Registry (ACTRN12609000502235).

**Figure 1 F1:**
[figure not shown]
Study design

All subjects will undergo a baseline assessment and re-assessment at 12 and 24 weeks. Following baseline assessment, stratified randomisation to the exercise or control group will be performed. Permuted block randomisation with block sizes of 4 will be used [29]. In order to achieve groups balanced for exercise capacity, subjects will be stratified based on the peak VO_2 _> or ≤ 70% of predicted values [30].

Subjects in both groups will receive usual medical care. Subjects randomised to the exercise group will undergo a 12 week, individually prescribed, supervised, outpatient exercise training program, followed by a 12 week home exercise program.

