### Assessment Procedures

Researchers 'blinded' to the subject's group allocation will perform all followup assessments. Each subject will undergo the following procedures at baseline assessment and again at 12 and 24 weeks. Subjects will be required to attend 3 assessment visits within a 2 week period, with each visit separated by at least 24 hours.

#### Visit 1

Subjects will undergo:

(i) Two unencouraged 6-minute walk tests (separated by a rest period of at least 30 minutes) that include monitoring of HR via telemetry (Polar FS3C heart rate monitor, Sportstek, Victoria, Australia), oxygen saturation (SpO_2_) (Respironics 512 pulse oximeter and finger sensor, Philips, Massachusetts, United States) and assessment of symptoms (Borg CR10 [31] dyspnoea and rating of perceived exertion [RPE]).

(ii) Familiarisation with the cycle ergometer and gas analysis equipment.

(iii) HRQoL assessment using the CAMPHOR [32], which has been recently validated in the Australian PAH population [33], and the Medical Outcomes Study Short Form 36 (SF36) Version 2 [34].

(iv) Assessment of physical activity using the International Physical Activity Questionnaire [35].

#### Visit 2

An incremental cardiopulmonary exercise test (CPET) using a continuous ramp protocol (Lode Corival cycle ergometer, Lode, Groningen, Netherlands) [36], to volitional exhaustion with breath by breath gas exchange analysis (Medical Graphics CPX-D, Medgraphics, Minnesota, United States) will be carried out. The test protocol will comprise 3 minutes of upright rest on the bicycle, followed by 3 minutes of unloaded pedalling (0 W). Subsequent workloads will be increased by 5 W/min, 10 W/min or 15 W/min increments depending on the subject's age, gender, weight, 6MWD and diffusing capacity of the lung for carbon monoxide (DLCO) [30]. The aim will be to achieve a test duration of 8 to 12 minutes from commencement of the incremental phase of the test to peak exercise due to volitional task cessation or symptom limitation. Standard criteria will be used to determine if test termination is required for safety reasons [36].

#### Visit 3

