### Sample size calculation

Improvements in endurance time following exercise training have recently been reported in the PAH population [10]. These authors [10] reported a mean increase in endurance time, as measured from a constant workload cycle ergometer test, of 270 seconds. The constant workload tests were set at 75% of the peak workload achieved during the incremental CPET, which is consistent with our study's protocol. The mean endurance time (standard deviation) at baseline and post-training were 390 (40) and 660 (60) seconds respectively.

Conservative sample size calculations have been performed using a two-sided Mann-Whitney U test, assuming that the actual distribution is a double exponential. Group sizes of 14 will achieve 91% power to detect a difference of 200 seconds between the null hypothesis that both group means are 600 seconds and the alternative hypothesis that the mean of group 2 is 400 seconds with estimated group standard deviations of 180 and 120 and with a significance level (alpha) of 0.01.

A total of 34 subjects (17 in the exercise group and 17 controls) will be recruited to allow for 20% attrition of subjects from the per protocol analysis.

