### Statistical methods

Data will be analysed using SPSS software (Version 17.0; SPSS Inc; Chi). Data that are not normally distributed will be transformed and if transformation fails to satisfy normality, non-parametric tests will be used. The primary and secondary outcomes in the exercise and control groups will be compared using two-way analysis of variance to account for group and time interactions. Statistical relationships between outcome variables will be analysed using Pearson's or Spearman's correlations as appropriate. Data will be analysed using (i) per protocol analysis and (ii) intention-to-treat analysis. Per protocol analysis will be restricted to the data from subjects who complete all assessments and for the exercise group who attend at least 75% of their exercise classes. The required number of sessions must be achieved within a period of 15 weeks for both the supervised and home exercise training programs, allowing for intercurrent illness and other factors that may impact on an individual's ability to attend sessions. The last-observation-carried-forward method will be used to impute missing data at 12 and 24 weeks for the intention-to-treat analysis [41]. The Berger-Exner [42] test will be carried out to determine whether selection bias has been introduced into the study.

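### A single disclosed block size of 4 makes up to about a third of assignments certain to anyone who knows the earlier ones, and a non-significant Berger-Exner test at n = 34 could not rule out selection bias

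*Protocol article*

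**What the plan says.** All references are to the Protocol article.

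- **Recruitment and Randomisation:** "Permuted block randomisation with block sizes of 4 will be used". No other block size is mentioned. There are two strata, peak VO2 above 70% of predicted and peak VO2 at or below it. On timing and method: after the baseline assessment, "stratified randomisation to the exercise or control group will be performed".
- **Participants:** "Thirty-four subjects will be recruited from the Western Australian State Pulmonary Hypertension Service", which is one service at one hospital.
- **Sample size calculation:** "A total of 34 subjects (17 in the exercise group and 17 controls) will be recruited".
- **Design:** "This study is a prospective, single blind, randomised controlled trial". **Assessment Procedures** says who is blinded: "Researchers 'blinded' to the subject's group allocation will perform all followup assessments". Blinding is not stated for recruitment or baseline testing.
- **Exercise group:** three supervised outpatient classes a week for 12 weeks, against usual medical care in the control group.
- **Statistical methods:** a Berger-Exner "test will be carried out to determine whether selection bias has been introduced into the study". No significance level, power or consequence of a positive result is given.

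**The concern.** With a constant block of 4, the last place in every block is fixed by the first three. The last two places are fixed whenever the first two went to the same arm. Someone who knows the block size and the earlier allocations in a stratum can therefore sometimes name the next assignment before it is made. Here the size is published, one service recruits everyone, and class attendance shows who is in the exercise arm.

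There is also room for discretion before allocation. Eligibility includes matters of judgement, such as willingness to complete the programs, stability of symptoms, and conditions that may limit exercise. If more motivated patients were entered when an exercise place was expected, effort-dependent outcomes such as endurance time could favour exercise without a training effect.

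The plan recognises the risk, since it includes a selection-bias test. That test is applied afterwards and prevents nothing. What matters is how much a non-significant result from 34 subjects can tell the reader.

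**Working it through.** **Inputs from the document:** block size 4, two strata, N = 34, 1:1 allocation. The document gives no figure for predictability or for the power of the Berger-Exner test, so there is no stated figure to reproduce on this point.

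**Assumptions:** the observer knows the block size, all earlier assignments in the stratum and the candidate's stratum. Steering shifts the outcome by +d when exercise is expected and by -d when control is expected, with d from 0.25 to 1.0 SD. The Berger-Exner test is two-sided at 5%.

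**1. Certain assignments in a complete block.** There are 6 equally likely orders of two exercise and two control places, hence 24 positions.
- Positions 1 and 2 are never certain.
- Position 3 is certain when the first two match, which happens in 2 of 6 orders, so 1/3.
- Position 4 is always certain.
- Share certain: (0 + 0 + 1/3 + 1)/4 = 33.3%, or 8 of 24.

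**2. Best guess.** The chances of being right are 1/2, 2/3, 2/3 and 1, with mean 70.8%.

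**3. Incomplete last blocks.** Applying step 1 to 34 subjects over every possible split between the strata gives 10.0 to 10.67 certain assignments. That is 10.0/34 = 29% to 10.67/34 = 31%. With 17 per stratum the best guess is right about 70% of the time.

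**4. Bias in an unadjusted follow-up comparison, complete blocks.**
- Steering on certain places only: 2 × d × 1/3, which is 0.167 SD at d = 0.25 and 0.333 SD at d = 0.5.
- Steering on every favoured guess: the excess of right over wrong guesses is 2 × 0.708 - 1 = 5/12, so the bias is 2 × d × 5/12, which is 0.208 and 0.417 SD.

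**5. Simulation.** 4,000 trials per setting, n = 34, two strata. The Berger-Exner test was run as a regression of outcome on treatment and reverse propensity score. The last column is the false-positive rate of a 5% t-test on follow-up values when there is no treatment effect.

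| Steering on | d (SD) | Berger-Exner power | Bias (SD) | False positives |
|---|---|---|---|---|
| certain places | 0.25 | 9% | 0.16 | 7% |
| certain places | 0.5 | 21% | 0.31 | 13% |
| certain places | 0.75 | 41% | 0.48 | 24% |
| certain places | 1.0 | 65% | 0.62 | 35% |
| every favoured guess | 0.25 | 12% | 0.20 | 8% |
| every favoured guess | 0.5 | 29% | 0.40 | 19% |
| every favoured guess | 0.75 | 58% | 0.60 | 32% |
| every favoured guess | 1.0 | 79% | 0.80 | 48% |

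A one-sided 5% test has 31-41% power at 0.5 SD and 76-88% at 1 SD. With 28 subjects (14 per group), two-sided power is 18-25% at 0.5 SD and 55-69% at 1 SD.

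**6. Effect of the planned analysis.** Statistical methods specifies a two-way analysis of variance for group and time. If steering adds a constant s to a subject's value at baseline and at follow-up, the change is (follow-up + s) - (baseline + s), and s drops out of the interaction. The biases in steps 4 and 5 therefore do not carry over to steering on stable fitness. They apply to characteristics that alter the response after baseline, such as motivation.

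**7. Alternative list.** Block sizes 4 and 6 are mixed with equal probability, 17 subjects per stratum, and the observer knows only which sizes are possible. Simulated certain assignments fall from 31% to about 6%. The best guess falls only from about 70% to 68%.

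**The case against.** A reader might infer that recruiters in this trial can foresee a third of the assignments. The document does not support that. It does not say who recruits, who holds the list or what recruiters see, and a condensed article commonly leaves concealment to the full protocol. That the allocations become visible to recruiters is an inference from the nature of the arms and from blinding that is stated only for follow-up assessors.

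Timing narrows the opportunity further. The stratum depends on the Visit 2 exercise test, so at consent it can only be guessed. Steering after that would mean dropping or delaying a subject already consented and tested, and a drop should show in the CONSORT-style flow. One third is therefore a ceiling.

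A reader might also infer that the Berger-Exner test is useless here, or that the authors intend to treat a non-significant result as proof of no bias. Neither follows. Power reaches 65-79% at 1 SD, and the article does not say how a non-significant result will be read.

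Finally, a reader might carry the bias and false-positive figures straight over to the planned analysis. They describe an unadjusted comparison at follow-up, and steering on stable fitness would largely cancel, as step 6 of the working shows. Small blocks also serve a legitimate purpose with 34 subjects in two strata.

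These limits stand. What remains is that concealing the next assignment does not hide what a known fixed block and visible earlier allocations reveal, and that the check has low power against small to moderate steering.

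**Conclusion.** The point holds as a conditional weakness in a stated design rule. It does not show that selection bias will occur.

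- **Predictability:** up to 33.3% of assignments are certain in complete blocks and 29-31% of 34 in this trial. This holds only if recruiting staff know the block size, the earlier allocations in the stratum and the candidate's stratum.
- **Detection:** about 9-29% power for assumed steering of 0.25-0.5 SD and 65-79% at 1 SD, two-sided 5%. A non-significant Berger-Exner result cannot establish that selection bias is absent.
- **Consequence:** assumed steering of 0.5 SD would bias an unadjusted follow-up comparison by about 0.3-0.4 SD and raise a nominal 5% false-positive rate to about 13-19%. In the planned group-by-time analysis the concern is confined mainly to steering on characteristics that affect later response.

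The size of any steering is an assumption, since nothing in the document sets it. The change is worth making because it is cheap.

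**What to change.** - For the remaining allocations, generate a new list with randomly varied block sizes (for example 4 and 6) within each stratum, and withhold sizes and order from recruiting staff. Simply enlarging the fixed block does much less: a known fixed block of 6 still leaves 25% of assignments certain in complete blocks.
- Report the Berger-Exner result descriptively, with a statement that a non-significant result is not evidence that selection bias is absent.

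**Cost:** a new allocation list. Imbalance within a stratum could be slightly greater, because an unfinished block of 6 can leave a difference of 3 between arms, against 2 for a block of 4. The gain lies in removing certainty. Best-guess accuracy barely changes, so the new list reduces the opportunity for steering and does not abolish it. If allocation is already complete, only the reporting change applies.
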